### Randomisation

A computerized random number generator draws up an allocation schedule prestratified for midwifery practice; within practices respondents are allocated to the intervention group or to the control group at random. During the first telephone call with the research assistants – 2 weeks after the first appointment with the midwife; at 10–14 weeks of pregnancy – participants are informed about which group they are assigned to.

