### Intervention

The New life(style) intervention program consists of 5 individual counselling modules together with a general information brochure. In the modules the counsellors discuss with the women allocated to the intervention group, how to control their weight during and after pregnancy, and how to maintain or optimize a healthy lifestyle in a period of drastic physical and mental changes. Women go through these counselling sessions in 30 weeks; they have appointments with their counsellor at 18, 22, 30 and 36 weeks of pregnancy and at 8 weeks postpartum. The counsellors, in charge of these counselling sessions, are members of the research team (see Counsellors). They are permanently linked to a specific midwifery practice. In this way, all women in the intervention group are assigned to a personal counsellor, facilitating the contact between participant and counsellor. Each counselling session takes 15 minutes, but the first session takes approximately half an hour, to explain the aim of the study and the intervention. The content of the first module is generalised and summarised in an information brochure, which the participants receive after the first counselling session of the intervention program.

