### Blood samples

In order to study the influence of lifestyle factors on energy homeostasis and weight gain, blood samples are taken intravenously from a subgroup of participants during each measurement. The midwives also take a blood sample from the umbilical cord. Blood is processed and stored at the laboratory of the VU University Medical Centre, so that – after selecting subgroups of normal and high gainers – blood levels of leptin, ghrelin, fasting insulin/glucose, insulin growth factor 1, insulin growth factor binding protein 1 and 3, and cortisol can be measured.

By means of the questionnaires, data are also collected on: perceived health, stage of change with regard to weight management, physical activity and diet according to the model of Prochaska, and behavioral determinants such as attitude, social support, self efficacy with regard to weight management, physical activity and nutrition. Possible confounders that are assessed include: age, age at menarche, education, ethnicity, marital status, smoking behaviour and individual health status, including complications during pregnancy, the duration of labour and possible complications during or after delivery.

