### Statistical analyses

Analyses will be performed to estimate the effect of the intervention on five domains: 1) total weight gain during pregnancy 2) the percentage of women gaining weight above the recommended IOM guidelines; 3) weight retention at six months and one year postpartum; 4) physical activity levels; and 5) behavioral determinants of weight management, physical activity and nutrition.

Longitudinal logistic regression analysis will be used for dichotomous outcome measures, and longitudinal linear regression analyses will be performed for all other outcome measures. In these analyses, the correlation between multiple measurements within one individual is taken into account. The regression coefficient reflects the average difference in the outcome variable between conditions. Possible confounders will be entered into the regression analyses. Confounding will be defined as a change in the regression coefficient of 10% or more. Possible effect modification will be studied as well, defined as a significant (p <0.10) interaction-term between group allocation and the variable concerned. Datawill be analysed according to the intention-to-treat principle and the per protocol principle.

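### The list of possible confounders includes labour, delivery and pregnancy events that follow allocation, and the 10% change rule can bring them into the intervention-effect model

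*Protocol article*

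**What the plan says.** The Statistical analyses section describes longitudinal linear and logistic models for five outcome domains. It first says what the coefficient of interest is: "The regression coefficient reflects the average difference in the outcome variable between conditions". The covariate rule follows directly: "Possible confounders will be entered into the regression analyses. Confounding will be defined as a change in the regression coefficient of 10% or more". Read in sequence, the rule acts on the group coefficient.

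The candidates are named at the end of the Blood samples section: "Possible confounders that are assessed include: age, age at menarche, education, ethnicity, marital status, smoking behaviour", followed in the same sentence by "individual health status, including complications during pregnancy, the duration of labour and possible complications during or after delivery". Stable traits and obstetric events share one list under one label.

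On timing, the Randomisation section says that during a telephone call at 10–14 weeks of pregnancy "participants are informed about which group they are assigned to". On the programme, the Intervention section says that "they have appointments with their counsellor at 18, 22, 30 and 36 weeks of pregnancy and at 8 weeks postpartum".

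The article does not limit the candidates to values fixed before allocation. It does not name an unadjusted analysis as primary, and it does not assign the obstetric variables to a separate analysis.

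**The concern.** Randomisation removes confounding by anything that precedes it. An event after allocation is not a cause of allocation, so it cannot confound the comparison. It can lie on the path from programme to outcome (a mediator), or share causes with the outcome while also responding to the programme (a collider). Adjusting for it changes the question from the effect of being offered the programme to something else.

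The 10% rule makes this more likely. A variable that carries part of the effect moves the group coefficient when it is added, and movement of that coefficient is the criterion for selection.

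The outcome domains differ. For weight gain in pregnancy and the share of women above the guideline, labour and delivery come at or after the end of the outcome period. They may be consequences of the outcome, so adjustment has no confounding rationale. For weight retention at six and twelve months they lie between allocation and outcome. At stake is whether the reported effects can be read as effects of randomisation.

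**Working it through.** **1. Frame taken from the plan.** Sample size section: difference 0.8 kg/m² in BMI at six months postpartum, SD 2.0, two-sided 5%, power 0.80, 110 per group. The plan has no figure on confounding to reproduce. Its inputs give 2 × (2.0 × (1.960 + 0.842) / 0.8)² = 98.1, so 99 per group. The stated 110 gives about 84% power. That gap is a separate matter; 110 per group is used below only as the setting.

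**2. What moves the coefficient.** In a linear model with a binary event M:

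unadjusted coefficient − adjusted coefficient = g × (event rate in programme arm − event rate in control arm),

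where g is the fitted effect of M on BMI. The rule selects M when the absolute change is at least 10% of the unadjusted coefficient, which is about 0.1 × 0.8 = 0.08 kg/m².

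**3. Assumed values (none are in the documents).** Control event rate 25%; programme-arm rate 25%, 20%, 15% or 10%; g from 1.0 to 2.0 kg/m²; true total effect −0.80. There is one event, one time point and a linear model, with 4000 simulated trials per setting.

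| Programme-arm rate | g | Selected by rule | Mean, unadjusted | Mean, always adjusted | Mean after rule |
|---|---|---|---|---|---|
| 25% | 1.0 | 21% | −0.80 | −0.80 | −0.80 |
| 25% | 2.0 | 50% | −0.80 | −0.80 | −0.80 |
| 20% | 1.0 | 32% | −0.80 | −0.75 | −0.76 |
| 20% | 2.0 | 66% | −0.79 | −0.69 | −0.70 |
| 15% | 1.0 | 59% | −0.80 | −0.70 | −0.72 |
| 15% | 2.0 | 89% | −0.80 | −0.60 | −0.60 |
| 10% | 1.0 | 81% | −0.80 | −0.65 | −0.66 |
| 10% | 2.0 | 99% | −0.80 | −0.50 | −0.50 |

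**4. Share removed.** Smallest shift: (0.795 − 0.764) / 0.795 = 3.9%. Largest: (0.802 − 0.500) / 0.802 = 37.7%. The range is about 4% to 38%.

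**5. Why selection also happens with no programme effect on the event.** With 25% in both arms, the SD of the difference in observed rates is √(2 × 0.25 × 0.75 / 110) = 0.058. With g = 2.0, a one-SD imbalance moves the coefficient by 2.0 × 0.058 = 0.117, above the 0.08 threshold. The event is then selected in about half of trials, with no mean bias.

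**6. Direction.** The shrinkage in the table follows from the assumed signs. If the event lowered BMI (g = −1.0) and the programme reduced it from 25% to 15%, the adjusted coefficient would be −0.8 − (−1.0) × (0.15 − 0.25) = −0.90, further from zero.

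**The case against.** **The link between the two sections is partly inferred.** The Blood samples list describes what the questionnaires collect, and the Statistical analyses section does not point back to it. The trial also has a stated aim on determinants of weight gain and retention, where labour and delivery data have a proper use. A fuller plan may narrow the candidates for each outcome. This is a reason to say that the text permits the adjustment rather than that it will occur. It does not remove the point: both sections use the same term, the list positively includes these events, and the rule is written for the between-group coefficient. If the text instead means that all candidates are entered whatever the 10% rule shows, the always-adjusted column applies.

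**Timing.** Some pregnancy complications could precede allocation at 10–14 weeks. That is correct for those; labour and delivery events cannot.

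**Stronger readings that a reader might infer, and that the documents do not support:**

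- *The bias is usually towards zero.* Nothing in the article fixes the sign, and step 6 shows the opposite case.
- *Power collapses.* With SE = 2.0 × √(2/110) = 0.2697, and 10%, 25% or 50% of the effect adjusted away, power would fall from 84% to 76%, 60% or 32%. These figures assume certain selection and an unchanged SE. The 50% case needs 0.40 kg/m² to run through the event. With a fall from 25% to 10% that means g = 0.40 / 0.15 = 2.67 kg/m², more than the SD. With a fall from 25% to 20% it means g = 8, whose variance contribution of 64 × 0.1875 = 12 exceeds the total variance of 4.
- *The 10% rule is also invalid for baseline covariates.* A simulation with 220 women and 10 assumed baseline covariates explaining 40% of variance gave type I error 0.035 under the rule, against 0.048 with the same covariates pre-specified. Power was 85% unadjusted, 92% under the rule and 96% pre-specified. For baseline covariates this is a secondary efficiency matter.

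**Conclusion.** The concern holds for events that follow allocation. The article labels them possible confounders and gives a rule that can admit them to the model for the randomised effect. This is a stated choice, not detail left to a fuller plan.

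Bias requires that the programme affects these events, including the case where they act as colliders. Without such an effect the mean estimate is right, but the adjusted model still turns on chance imbalance. Under the assumed rates and event effects, about 4–38% of a 0.8 kg/m² difference is removed, with selection in about 32–99% of trials. These sizes are illustrative: they rest on assumed values, cover one linear outcome at one time point, and do not extend to the logistic models.

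**What to change.** In Statistical analyses, state that length of labour, delivery and postpartum complications, and pregnancy complications arising after allocation are not adjusted for in any intervention-effect analysis. Use them only in determinant or mediation analyses labelled as such.

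For the randomised comparison, replace the 10% rule with one covariate set fixed in advance for all outcomes: midwifery practice (the stratification factor), pre-pregnancy or 15-week weight or BMI, and, if wanted, stable traits such as age and education.

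The restriction should not be worded as a ban on everything recorded after randomisation. Women learn their group at 10–14 weeks and the baseline visit is at 15 weeks, so that wording would exclude the trial's own baseline. The 15-week measurement still precedes the first counselling session at 18 weeks.

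The cost is a change of wording and a small loss of flexibility in covariate choice. These covariates need no new data, and the sample size is unaffected.

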## Discussion

The New Life(style) intervention program is designed to fill the gaps that currently exist for public health professionals with regard to providing guidance for pregnant women who have difficulties with controlling their weight gain during pregnancy. As a result of the close cooperation with the participating midwife practices in this study, we are able to reach a representative study population of women who are expecting their first child. Furthermore, the counselling sessions of participants in the intervention group and the measurements of all participants are performed in these practices, hereby minimising the burden for women who participate in the study. Because of the personal and repetitive character the New Life(style) program is expected to be a helpful tool to help pregnant women to gain weight within IOM-guideline limits.

Results of the current RCT will improve insight in determinants of weight gain during pregnancy, weight retention after childbirth and in the effectiveness of the intervention program. If the New Life(style) intervention program proves to be an effective tool, a future update of the Dutch and/or international guidelines of midwifery care with the current protocol will be needed. Because of the fact that the counselling sessions in this study are provided by members of the research team, implementation of the New Life(style) protocol in the daily practice of midwifes will then need to receive further attention.
